### Data collection

The tests and questionnaires used for these assessments are listed along with their outcome variables in Fig 1. (The recommendations for Interventional Trials (SPIRIT) schedule of enrollment, interventions, and assessments).

**Fig 1 pone.0279310.g001:**
[figure not shown]
Template of recommended content for the schedule of enrolment, interventions and assessments. t1: before intervention; t2: after intervention; t3: 24 weeks follow-up; IMT: inspiratory muscle training; mMRC: Medical Research Council scale; BORG-D: dyspnea borg scale; BORG-F: fatigue borg scale; 6MWT: Six Minute Walk Test; MMSE: Mini Mental State Exam; SF-36: *Medical Outcomes Study 36-Item Short Health Form Survey;* IPAQ: *International Physical Activity Questionnaire*; SDS: Self-rating Depression Scale; SAS: Self-rating Anxiety Scale.

#### Clinical evaluation form

After signing the informed consent form, patients will be assessed using an evaluation form. This form will assist collection of personal data, vital signs, anthropometric measurements, personal and pathological background, lifestyle habits, physical examination (inspection and palpation), and complementary exams.

#### Respiratory muscle strength

Respiratory muscle strength will be assessed by measuring MIP and maximal expiratory pressure (MEP) using an analog manovacuometer (GERAR^®^, São Paulo, Brazil).

Patients will use a nasal clip and remain seated comfortably in a chair with back support, hip angle of 90°, upper limbs resting on legs, and feet on floor. To measure MIP, patients will perform maximal expiration until residual volume, place the mouthpiece, and perform a maximal inspiratory effort against an occluded airway, and sustain for a minimum of one second. To measure MEP, the patient will inspire close to total lung capacity, place the mouthpiece, and perform a maximal expiratory effort against the occluded airway, maintaining for at least one second [14]. Patients will be constantly encouraged by the researcher during the test.

For data analysis, at least three reproducible maneuvers will be performed with variability lower than 20%; the highest value will be registered. References values for the Brazilian population will be calculated according to age and gender [14].

#### Pulmonary function

Pulmonary volume and capacity will be evaluated using a calibrated spirometer (Koko Digidoser model, Spide, Longmont, USA) in an acclimatized room. Patients will be advised to avoid large meals one hour before the test, food and drinks with caffeine for at least six hours before the test, and alcoholic drinks on the day of the test [15].

The test will consist in performing an inspiratory maneuver until total lung capacity, followed by maximal and forced expiration to residual volume using the spirometer. Tests will be performed with patients seated and hips and ankles flexed at 90º [13]. A minimum of three tests will be conducted with variation less than 5%; the highest forced expiratory volume in the first second and forced vital capacity obtained will be compared with predicted values for the Brazilian population [16].

#### Dyspnea

Dyspnea will be assessed using the Medical Research Council scale adapted to Portuguese. Patients must indicate the impact of dyspnea on mobility during daily activities. Scores range between 1 and 5, and highest values indicate greater dyspnea [17].

#### Perception of effort and fatigue

Patients will be questioned about subjective perception of respiratory effort and lower limb fatigue before and after training using the modified Borg rating of perceived exertion (10-Borg) scale. Higher values correspond to greater sensation of dyspnea.

#### Handgrip strength

Handgrip strength will be measured using a hydraulic handheld dynamometer (Saehan®). Maximal isometric strength of the dominant hand will be assessed with patients seated comfortably in a chair, with knee and ankle joints at 90º, shoulder of dominant arm forward and in neutral rotation, elbow flexed at 90º near upper body, forearm in neutral position, and wrist between 0º to 30º of extension and 0º to 15º of ulnar deviation. Participants will be requested to perform maximal isometric strength for five seconds without moving other body parts [18]. Three measurements will be performed with one-minute interval in between, and the average will be considered for analysis. Patients will be considered fragile if the average of three measurements is between 20% of lower distribution values, according to the World Health Organization [19, 20].

#### Six-minute walking test

The 6MWT evaluates submaximal functional capacity by measuring the distance walked on a 30-meter flat surface for six minutes. Patients will be instructed to walk as fast as possible without running and stop to rest when needed. The researcher will monitor heart rate, oxygen saturation, dyspnea, and lower limb fatigue at each lap. Standardized verbal stimulus will be given every minute, as recommended (ATS, 2002). The distance walked after six minutes and predicted values based on gender, weight, age, and height will be included for analysis [21].

Arterial blood pressure, heart rate, oxygen saturation, and Borg will also be assessed before and after the test. The test will be interrupted if patients present chest pain, intolerable dyspnea, oxygen saturation < 85%, cramps, sweating, paleness, or vertigo [21].

#### Cognitive evaluation

The MMSE will be used to screen cognitive function. The test consists of two sections that assess orientation to time, orientation to place, registration, calculation, repetition, 3-step command, reading and obeying, recall, naming, writing, and copying. Total score ranges from 0 to 30, and higher scores indicate better cognitive performance [22]. Cut-off points will be used to minimize the influence of educational level in total scores [23].

#### Medical outcomes study 36-item short health form survey

The Medical Outcomes Study 36-Item Short Health Form Survey (SF-36) is a multidimensional questionnaire translated and validated to the Brazilian population [24, 25]. SF-36 evaluates health-related quality of life using 36 items distributed into eight domains. These domains encompass two components: physical (physical aspects, bodily pain, general health status, and physical functioning) and mental (emotional status, social functioning, mental health, and vitality). Subscale score ranges from 0 to 100, and higher scores indicate better health-related quality of life [26].

#### International physical activity questionnaire

The extended version of the International Physical Activity Questionnaire (IPAQ), adapted [25] and validated to the Brazilian population [28], will be used to assess duration and frequency of moderate or vigorous physical activities in the last seven days. It comprises 15 questions divided into five domains: job-related, transportation, household, recreation, and leisure.

Trained evaluators will apply the IPAQ as an interview, and older people must answer the questionnaire considering the actual week. Energy expenditure for each activity will be estimated in metabolic equivalents considering minutes of physical activity performed per week [27–29]. The people will be classified as very active, active, irregularly active, or sedentary [30].

#### Depression and anxiety scale

The self-rating depression scale (SDS) and the self-rating anxiety scale (SAS) will be used to screen patients for depression and anxiety, respectively. SDS and SAS have 20 items with scores ranging from 1 to 4; higher scores indicate higher severity of depression and anxiety [31].

#### Post-COVID-19 functional status scale

The post-COVID-19 functional status scale analyzes relevant aspects of daily life after the infection. The scale assists users in recognizing current functional limitations post-COVID-19 and determines the degree of functional limitations. It contains six items ranging from 0 to 5 that cover functional outcomes focusing on limitations in activities of daily living (e.g., household activities, professional/study activities, and lifestyle changes). Higher scores indicate worst functional status [32].

#### Adverse effects and adherence

Adverse effects and adherence will be assessed using a training diary will be given to all patients to assess adverse effects and adherence. After all training sessions, they will be encouraged to fill the diary, registering positive and negative observations and complications during and after training. Adherence will be assessed considering every time patients register the realization of the session. Fulfilled sessions will be added and then divided by the total number of sessions patients could perform.

Adherence to training will be considered by verifying the number of days that patients performed the sessions. The sum of all sessions performed will be divided by the total number of sessions that patients must perform. Adverse effects will consider all complications registered in the diary or mentioned during final evaluations.

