### Exclusion criteria

Patients with conditions impairing assessments, health complications that justify interrupting data collection (e.g., syncope, intense chest pain, or cough with blood-tinged sputum), hospitalized due to exacerbation of clinical conditions, or requested to leave the study will be excluded.

Regarding recruitment, researchers will contact the Hospital Giselda Trigueiro and inform patients about the study.

The sample will be randomized (www.randomization.com) in two groups: active (AG, IMT with load) and SHAM (SG, placebo IMT without load). Groups will be coded, and allocation will be included in sealed and opaque envelopes numbered consecutively.

This study will include three investigators: the first will be responsible for assessments; the second, adjustment of training load; and the third, randomization. This is a double-blinded study because the first researcher and patients will be blinded to allocation of patients and intervention effects.

This protocol was approved by the research ethics committee of Universidade Federal do Rio Grande do Norte (Brazil) (CAAE**:** 45575421.7.0000.5537) on May 1, 2021 and submitted to Clinical Trials (NCT05077241). Autonomy and anonymity of patients will be respected, ensuring personal data privacy according to resolution nº 510/16 of the National Health Council and Declaration of Helsinki. Before entering the study, all patients will sign the informed consent form.

Our study was written in accordance with Standard Protocol Items: Recommendations for Interventional Trials (SPIRIT), which was aim to improve the quality of clinical trial (S1 Checklist).

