### Interventions

Patients included will be evaluated in three moments: pre-training (initial), post-training (six weeks after pre-training), and retention (24 weeks after pre-training). After recruitment, one researcher previously trained and blinded to allocation will evaluate vital signs, anthropometric measurements, pulmonary volume, respiratory muscle strength, handgrip strength, quality of life, anxiety, depression, functional status, and functional capacity.

After initial evaluation, all patients will receive a POWERbreathe® (POWERbreathe®, HaB Ltd, Southam, UK) device and be individually oriented on how to perform the IMT protocol. An experimental session will be conducted for familiarization with the device. Patients will receive a phone call every three days from the second researcher (who will not participate in the evaluation) to confirm if IMT is being performed correctly and resolve doubts regarding the protocol. At the end of each week, patients from EG will receive a video call from the second researcher to adjust load of the device.

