#### Intervention protocol

The following training protocols will be applied.

Active group protocol: IMT using 30% of MIP and load increase of 10% of initial MIP every week. Patients will perform 30 repetitions, twice a day (morning and afternoon), for seven consecutive days, and six weeks. Patients will be instructed to perform a fast inspiratory muscle contraction, sustain it for two seconds, and expire. Thirty seconds of rest will be allowed every three IMT repetitions to avoid muscle fatigue or complications.

Sham group protocol: patients will use an IMT device without load and receive the same instructions as EG. If the treatment applied to EG be effective, we will invite patients from CG at the end of the study to perform the IMT protocol with load.

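### The adverse-effect definition names only the diary and the final evaluations, so the events that cause a patient's removal can be lost from the safety result

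*Protocol article*

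**What the plan says.** The section on adverse effects and adherence in the Protocol article gives every patient a training diary. After each session "they will be encouraged to fill the diary, registering positive and negative observations and complications during and after training". It then states what makes up the result: "Adverse effects will consider all complications registered in the diary or mentioned during final evaluations". The text shown names no other source.

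Two other sections bear on this rule.

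- **Exclusion criteria.** Patients are excluded for "health complications that justify interrupting data collection (e.g., syncope, intense chest pain, or cough with blood-tinged sputum" (the list is of examples). The same sentence adds patients "hospitalized due to exacerbation of clinical conditions, or requested to leave the study will be excluded".
- **Interventions.** "Patients will receive a phone call every three days from the second researcher", and the purpose given is "to confirm if IMT is being performed correctly and resolve doubts regarding the protocol". In addition, at the end of each week, "patients from EG will receive a video call from the second researcher to adjust load of the device". The label EG is not defined in the article. It is read here as the active arm, since only that arm has a load to adjust.

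**The concern.** The two named sources are weakest for the patients who matter most to a safety result. A diary filled in by the patient and only encouraged is easily left blank by someone who has just fainted or been admitted to hospital. The other source, the final evaluation, may not take place for a patient whose data collection has been interrupted. The reason for removal, which the study team would normally know, is not among the things counted.

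Training is done at home, and the load rises weekly in the active arm only. If complications of loaded training led to removal, the uncounted events would fall more in that arm, and the comparison between arms would be affected as well as the total. Any later statement about tolerability would then lean on those who stayed in the study.

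**Working it through.** The article states no safety figure and no final sample size (that awaits the pilot), so there is no planned number to reproduce. The check is a comparison of sections plus one division.

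**Step 1: does the exclusion rule act after enrolment?** It sits under a heading that usually covers eligibility. However, interrupting data collection and asking to leave can only happen to someone already in the study. The rule therefore covers removal during follow-up.

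**Step 2: which route carries each event into the result under the stated definition?**

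| Event | Diary | Final evaluation | Counted as written? |
|---|---|---|---|
| Complication in a patient who completes | If the patient writes it down | If the patient mentions it | Yes, by either route |
| Complication told to the caller only | No | Only if repeated there | Not unless repeated or written down |
| Event that causes removal or hospitalisation | If written down before or despite removal | Not stated that one takes place | Only if written down, or if an evaluation is still held |
| Reason for a requested withdrawal, where it is a complication | If written down | Not stated that one takes place | Same as above |

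The last two rows are the gap. For these patients the diary, which is voluntary, may be the only source left.

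**Step 3: how much staff contact is not named as a source?** The training period is 7 days a week "for seven consecutive days, and six weeks", so 7 x 6 = 42 days. With one call every three days, 42 / 3 = 14 phone calls per patient, in both arms. This counts contacts, not lost events: a complication told to the caller may also be in the diary or be repeated later.

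**Step 4: are all the contacts equal between arms?** The phone calls are. The weekly video calls are not: at one per week for six weeks, the active arm has up to 6 extra contacts and the sham arm none. Counting events that come to light only in video calls would give the active arm more chances to report.

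**Step 5: who is blinded?** The article names the first researcher (the assessor) and the patients. The phone calls are made by the second researcher, who also adjusts the load and is not among those stated to be blinded.

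**The case against.** The strongest reply is that the defining sentence does not contain the word *only*, and nothing in the article says that an event learned another way is thrown out. An article condenses a longer protocol, which may well hold the rules for serious events and withdrawals. This stands in part: the article does not prove that such events will be discarded. But it does not leave the matter open either. It states what adverse effects will consist of, lists two sources, and no other section adds a third. That is a rule fixed too narrowly, not detail left out.

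A reader might infer that removed patients certainly have no final evaluation, and that the safety result is therefore biased downwards. The documents do not support that. No section says that these patients are not evaluated, and diary entries already made still count. Loss is possible, not certain. That removals would fall mainly in the active arm is likewise a possibility and not something the article shows.

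A reader might also combine the 20% dropout allowance in the sample-size paragraph with assumed event rates to estimate the share of affected patients missed. That would not be sound. The documents give no event rate. The 20% is an allowance for dropout from any cause with no time point, and follow-up runs to 24 weeks. A patient lost after week six may already have finished the diary and had the post-training evaluation.

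It is also fair to say that adverse effects are neither a primary nor a secondary outcome and that the statistical section names no safety comparison. This limits the stakes: the efficacy analysis is untouched. It does not justify leaving a definition that can miss the most serious events.

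Finally, using the calls has a price. The diary and the assessor's evaluations rest on people stated to be blinded, and the caller is not. That objection stands, and the fix has to deal with it.

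**Conclusion.** The point holds in a limited form. As written, the definition can leave out the event that led to a patient's exclusion, withdrawal or hospitalisation, and it does not name about 14 phone calls per patient as a source. The loss could differ between arms. No size can be put on it from the documents, and no direction of bias is established.

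The conclusion rests on three readings: that the two listed sources are meant as the full list, that the exclusion rule applies after enrolment, and that a removed patient may have no final evaluation. The second follows from the wording. The first and third are the natural reading, but the full protocol, which is not shown, could change them. Because the repair is cheap and makes the safety result more complete, the change should be made.

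**What to change.** Reword the defining sentence under Adverse effects and adherence so that, besides the diary and the final evaluations, adverse effects include:

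1. the reason for any exclusion, withdrawal or hospitalisation after randomisation;
2. any complication a patient reports in the three-day phone calls, asked with one identical scripted question in both arms.

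Do not count events reported only in the weekly video calls in the comparison between arms, because only the active arm receives those calls.

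Report the number of patients with at least one event by arm, over all randomised patients, including those removed under the Exclusion criteria section. Show events by source, so that a reader can see what each route contributes.

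The cost is some rewording and one question added to calls already planned, with no extra staff or visits. There are two downsides to state. Reported counts may be somewhat higher and the calls slightly longer. And the caller adjusts the active arm's load and is not stated to be blinded, so answers should be recorded verbatim and classified by the blinded assessor. This reduces the risk of unequal recording but does not remove it, which is a further reason to show events by source.

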#### Intervention protocol

The following training protocols will be applied.

Active group protocol: IMT using 30% of MIP and load increase of 10% of initial MIP every week. Patients will perform 30 repetitions, twice a day (morning and afternoon), for seven consecutive days, and six weeks. Patients will be instructed to perform a fast inspiratory muscle contraction, sustain it for two seconds, and expire. Thirty seconds of rest will be allowed every three IMT repetitions to avoid muscle fatigue or complications.

Sham group protocol: patients will use an IMT device without load and receive the same instructions as EG. If the treatment applied to EG be effective, we will invite patients from CG at the end of the study to perform the IMT protocol with load.

### Statistical analysis

SPSS software version 22.0 (IBM Corp. USA) will be used for data analysis. Normality will be verified using Shapiro-Wilk or Kolmogorov-Smirnov, according to the number of patients included. Variables presenting nonparametric distribution will be compared using Wilcoxon (intragroup analysis) and Mann-Whitney test (intergroup analysis), whereas repeated measures two-way ANOVA will be performed in case of parametric distribution. Dunn’s post hoc test will be used to identify significant differences in the two-way ANOVA test.

Descriptive analyses will be conducted using mean and standard deviation or median and interquartile range (25% - 75%), according to data distribution. A significance level of 5% will be applied to minimize type I error. The power of the study and effect size will also be performed for the main results of the study.

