**Primary outcomes:**

Respiratory muscle strength, dyspnea, and quality of life of post-COVID-19 patients.

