## Material and methods

### Type of study and location of research

This randomized, controlled, double-blind, parallel, two arm clinical trial will be conducted at the Instituto de Medicina Tropical and of Universidade Federal do Rio Grande do Norte, referred from the ambulatory of infectology of Hospital Giselda Trigueiro (Rio Grande do Norte, Brazil) will be recruited.

Sample size will be determined using maximal inspiratory pressure (MIP) (GPower Software version 3.1.9.2, Kiel, Germany) after a pilot study with five patients in each group (total of 10 patients). Mean and standard deviation will be used to estimate effect size, and a bilateral distribution with alpha error of 0.05 and 80% power will be adopted. Sample size will be adjusted assuming a dropout rate of 20%.

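### A normality test on the trial's own data picks the test and effect measure for the continuous primary outcomes, so neither is fixed in advance

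*Protocol article*

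**What the plan says.** The Abstract lists the primary outcomes as "Respiratory muscle strength, dyspnea, and quality of life of post-COVID-19 patients". The Statistical analysis section, which the Abstract repeats, handles every variable by one rule:

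- The gate: "Normality will be verified using Shapiro-Wilk or Kolmogorov-Smirnov, according to the number of patients included".
- If normality fails: "Variables presenting nonparametric distribution will be compared using Wilcoxon (intragroup analysis) and Mann-Whitney test (intergroup analysis".
- If it does not: "whereas repeated measures two-way ANOVA will be performed in case of parametric distribution".
- Summaries switch as well: "Descriptive analyses will be conducted using mean and standard deviation or median and interquartile range (25% - 75%), according to data distribution".

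The sample size is to be based on MIP "after a pilot study with five patients in each group (total of 10 patients". The inputs to that step are given under Type of study and location of research: "Mean and standard deviation will be used to estimate effect size, and a bilateral distribution with alpha error of 0.05 and 80% power will be" [...].

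The text does not say what the normality test is applied to (each arm, each visit, pooled data or residuals), at what sample size one normality test replaces the other, or whether Mann-Whitney is run on post-training values or on change.

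**The concern.** The two branches do not estimate the same thing. The ANOVA branch compares means over three visits and offers a group-by-time contrast. The rank branch compares the arms by rank and tests change within each arm separately. As written it contains no group-by-time contrast, unless Mann-Whitney is meant to be applied to change. A reader of the protocol therefore cannot say whether the MIP result will be a difference in means or a rank comparison reported with medians.

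The gate also responds to sample size more than to need. It has little power to detect non-normality in small samples, where the shape matters most. It detects mild skew in large samples, where a comparison of means is robust.

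At stake are the effect measure and the planned power. The sample-size step is built on a mean and SD, but the data decide whether means are compared at all.

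**Working it through.** **Inputs.** From the protocol: three visits (before training, six weeks, 24 weeks), two arms, two-sided alpha 0.05, power 80%. It gives no N, effect size, SD or correlation, so there is no planned figure to reproduce. Assumed for illustration: standardised difference d=0.8 at both post-training visits, the same correlation r between all visits, r = 0.3, 0.5 or 0.7, and normality tests at the 5% level.

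**Illustrative size.** n = 2(1.96+0.84)²/d² = 15.7/0.64 = 24.5, so 25 per arm by the normal approximation. A t-test needs about 26, the size used below.

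**1. Chance of switching when the data are exactly normal.** If the tests were independent, the chance of at least one rejection in k tests is 1−0.95^k.

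- Six cells (two arms × three visits): 1−0.95⁶ = 0.265. Simulation with correlated visits gives 24-27%.
- Three pooled visits: 1−0.95³ = 0.143. Simulation gives about 12-15%.

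**2. Power by branch, normal data, 26 per arm, d=0.8.**

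- Group-by-time F test: noncentrality λ = (n/2)(2d²/3)/(1−r) = 13×0.427/(1−r) = 7.9, 11.1 and 18.5 for r = 0.3, 0.5 and 0.7, on 2 and 100 df.
- Mann-Whitney on the six-week value: a t-test at d=0.8 with n×0.955 per arm, where 0.955 is the rank test's relative efficiency under normality.
- Mann-Whitney on change: the same, with d/√(2(1−r)) = 0.68, 0.80 and 1.03.

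| r | Group-by-time: formula / simulated | Mann-Whitney at six weeks: formula / simulated | Mann-Whitney on change: formula |
|---|---|---|---|
| 0.3 | 70% / 72% | 79% / 78% | 65% |
| 0.5 | 84% / 84% | 79% / 79% | 79% |
| 0.7 | 97% / 96% | 79% / 80% | 95% (simulated 94%) |

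The order of the branches reverses between r=0.3 and r=0.5. At r=0.7 most of the gap comes from ignoring baseline, because the rank test on change almost closes it.

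For comparison, ANCOVA at six weeks has effective difference d/√(1−r²) = 0.84, 0.92 and 1.12. That gives power of about 84%, 90% and 98%, at least as high as any column above at each r.

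**3. Dependence of the gate on sample size.** For a moderately skewed variable (assumed lognormal, CV 0.4), Shapiro-Wilk rejects in about 18%, 37%, 65% and 94% of samples at n = 10, 20, 40 and 80. At n=60 the choice of normality test matters too. Shapiro-Wilk rejects about 83-86%. Kolmogorov-Smirnov rejects about 52% with the Lilliefors correction and about 5-6% without it. The protocol does not say which version is meant.

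**4. Type I error.** With no treatment effect and normal data, the two-stage rule rejects in about 5% of trials.

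**5. Dyspnea grade.** On this scale, "Scores range between 1 and 5, and highest values indicate greater dyspnea". With assumed category probabilities 0.15/0.30/0.30/0.15/0.10 and all six cells required to pass, the ANOVA branch is reached in 9% of trials at 10 per arm, 0.5% at 17 and 0% at 26.

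**The case against.** The rule is mechanical and written down in advance, so it is not a free choice among results. Both branches compare active with sham training. A separate analysis plan may also exist. The first two statements are correct and limit the point. The third does not remove it, because the protocol states a rule and does not leave the matter open.

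Three stronger readings are tempting, and the material does not support them:

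- **That the rank branch loses power.** This holds at r=0.7 with Mann-Whitney on the six-week value, and it reverses at r=0.3. In a two-visit simulation with skewed data (lognormal, sigma 0.5) and r=0.3, Mann-Whitney had 90-94% power against 66-67% for group-by-time. The protocol gives no correlation and does not say whether values or changes are ranked.
- **That choosing the test from the data inflates false positives.** A reader might infer this, but the simulated type I error stayed near nominal.
- **That dyspnea could easily end up in an ANOVA.** At realistic sizes the grade goes almost surely to the rank branch, which suits it. What remains is that the method should follow from the five-level scale and not from a normality test.

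It is also fair to say that means are not the only defensible choice for SF-36 domains. They are bounded from 0 to 100 and may cluster at the ends.

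**Conclusion.** The point stands for the continuous primary outcomes: MIP, maximal expiratory pressure (MEP) and the SF-36 scores. Their test and effect measure are not fixed in advance, and the mean-based sample size for MIP is tied to a test that may not be used. Under the assumed 26 per arm and exactly normal data, about one trial in four would change branch by chance with cell-by-cell testing, and about one in seven with pooled visits. Power then shifts by an amount and in a direction that cannot be known beforehand: from about 6 points higher in the rank branch (r=0.3) to about 16 points lower (r=0.7), using six-week values at d=0.8.

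All these sizes rest on assumed d, r, N and distributions. The structural point rests on the text alone. The change is advisable, but the error rate is not broken.

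**What to change.** Delete the normality gate from the Statistical analysis section and the Abstract, and name one method per outcome before unblinding:

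- **MIP, and also MEP, six-minute walk distance, handgrip and spirometry:** one baseline-adjusted comparison of means, such as ANCOVA at six weeks or a mixed model with baseline. Base the sample size on the method named for MIP.
- **SF-36 domains:** one method named in advance, either means or a rank/ordinal method if clustering at the ends of the scale is expected.
- **Dyspnea and functional status grades:** one ordinal or rank method.

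Check residuals afterwards, and report a rank or bootstrap analysis as sensitivity only. The cost is rewording one paragraph and its copy in the Abstract. The small downside is that some skewed outcomes will be summarised by means, which the sensitivity analysis covers.
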